## Abstract

**Background:**

Traditional harvesting of the internal thoracic artery (ITA) for use as a conduit in coronary bypass surgery involves the dissection of a rim of tissue surrounding the artery on either side. Recent studies, primarily observational, have suggested that skeletonization of the ITA can improve conduit flow, increase length, and reduce the risk of deep sternal infection in high risk patients. Furthermore, skeletonization of the ITA can potentially preserve intercostal nerves and reduce post-operative pain and dysesthesias associated with ITA harvesting. In order to assess the effects of ITA skeletonization, we report a prospective, randomized, within-patient study design that shares many features of a cross-over study.

**Methods:**

Patients undergoing bilateral internal thoracic artery harvest will be randomized to having one side skeletonized and the other harvested in a non-skeletonized manner. Outcome measures include ITA flow and length measured intra-operatively, post-operative pain and dysesthesia, evaluated at discharge, four weeks, and three months post-operatively, and sternal perfusion assessed using single photon emission computed tomography. Harvest times as well as safety endpoints of ITA injury will be recorded.

**Discussion:**

This study design, using within-patient comparisons and paired analyses, minimizes the variability of the outcome measures, which is seldom possible in the evaluation of surgical techniques, with minimal chance of carryover effects that can hamper the interpretation of traditional cross-over studies. This study will provide a valid evaluation of clinically relevant effects of internal thoracic artery skeletonization in improving outcomes following coronary artery bypass surgery.

## Introduction

Coronary artery bypass surgery (CABG) remains the gold standard for the treatment of multi-vessel and left main coronary disease[1]. The use of the internal thoracic arteries (ITAs) as bypass conduits has been associated with improved long-term outcome following CABG[2,3]. Despite these long-term benefits, there are certain characteristics of the ITAs that limit their use in particular settings. The internal thoracic arteries can be prone to vasospasm and hypoperfusion in the early post-operative period, particularly in the presence of vasoactive medications[4,5]. Harvest of the ITAs is associated with impairment in sternal perfusion[6] and increased deep sternal wound infections[7], particularly in diabetic patients. The length of usable conduit available is often limited and ITA harvest has been associated with increased and persistent post-operative pain [8-10].

The traditional ITA harvesting technique involves the dissection of a rim of tissue (1 – 2 cm) around the ITA. Skeletonization of the ITA has been proposed as a solution to many of the problems associated with ITA harvesting. The skeletonization procedure, first described by Keeley et al in 1987[11], involves the harvest of only the ITA without any surrounding tissue. This technique requires meticulous dissection and carries the theoretical risk of increased arterial injury. However, studies to date have not demonstrated any differences in microscopic injury or vascular function when compared to non-skeletonized ITAs[12,13]. Numerous benefits of skeletonized ITA harvest have been proposed including increased flow[14] and length[12], as well as a decreased sternal infection rates[15], and reduced pain[16]. However, these assertions are supported primarily by non-randomized, observational studies. It is not surprising, therefore, that there is significant variation among surgeons as to the harvesting technique employed.

In order to evaluate the differences in skeletonized versus non-skeletonized ITA harvest, we propose the use of a paired study design to evaluate within-patient differences in ITA flow, length, sternal perfusion, and post-operative pain and dysesthesias.

## Methods

### Patient population

This study has been approved by the Institutional Review Board of the University of Ottawa Heart Institute. All patients undergoing isolated, non-emergent coronary artery bypass surgery using bilateral internal thoracic artery harvest by two surgeons will be screened for eligibility for this study. Exclusion criteria include known subclavian artery stenosis, non-fluency in English or French, and inability to complete follow-up visits. Of note, insulin-dependent diabetes, systemic steroid use, and morbid obesity remain relative contra-indications for bilateral non-skeletonized internal thoracic artery use at our institution.

### Study design, randomization, and blinding

This is a prospective, randomized study in which each patient receives both study interventions i.e. a skeletonized ITA and a non-skeletonized ITA. Patients are randomly allocated to receive a skeletonized ITA first followed by a non-skeletonized harvest or vice versa i.e. the order of treatments is randomly assigned. In addition, the randomization scheme is stratified by the side to which the intervention is applied in order to ensure equivalent numbers of left and right sided ITAs that are skeletonized. Randomization will be performed intra-operatively by opening a sealed, opaque envelope at the time of sternotomy which contains computer-generated random sequences assigned to each enrolled patient.

Patients will remain unaware of the treatment assignment throughout the course of the study. Assessment of the outcome measures will be performed by individuals blinded to the treatment assignment whenever possible. Because of the nature of certain endpoints, requiring visual feedback, evaluation of ITA length and flow will be performed intra-operatively by individuals performing the ITA harvest who will be aware of the treatment assignment.

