### Conduit length

The length of the harvested ITA will be measured in-situ (i.e. with the proximal and distal ends attached) from the first rib to ITA bifurcation in a standardized fashion. After the conduit has been fully dissected along its entire length and prior to division of its distal end, the midportion will be encircled by a length of sterile silk suture. Uniform tension will be applied to the two ends of the suture. A separate silk suture will then be used follow the course of the ITA to measure its length from the first rib to the ITA bifurcation. Separate sutures will be used for the left and right sides and labeled in order to avoid misclassification.

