### Conduit flow

ITA flow will be measured on four separate occasions. The first time point will be immediately following each individual ITA harvest with the vessel in-situ, using a Doppler flow meter (Transonics Inc., Binghamton, NY, USA). The flow probe will be placed at a point approximately halfway between the first rib and the ITA bifurcation. The size of the probe will be chosen by the surgeon to best fit the conduit and the same probe will be used for both ITAs in order to minimize variability and measurement error. The second measurement will be performed after both ITAs have been harvested, are ready for distal division and systemic heparin has been administered. Direct blood flow from each ITA will be measured upon division by measuring the amount of blood filling a calibrated cup over 15 seconds. The ITAs will then be treated with a vasodilator, papaverine, applied topically, in order to eliminate any vasospasm that may occur due to the handling as well as mechanical or thermal trauma to the vessel. The third flow measurement will be performed after a 5–10 minute treatment with papaverine (equal duration of treatment for both ITAs) using the direct flow technique described above. The patient will then undergo coronary artery bypass grafting and the final flow measurement will be performed after all anastomoses have been completed, using the Doppler flow probe.

The amount of flow within a vessel is a function of the systemic blood pressure and the resistance offered by the vessel. In addition, errors in measurement exist with all measuring devices including the transonic Doppler flow probe. Post-anastomotic Doppler flows are further dependent on the size of the outflow vessel, the degree of distal disease and the size and vasoreactive characteristics of the distal myocardial bed that is supplied. Recognizing these potential sources of inaccuracies, pre-anastomotic direct flow (before papaverine treatment) measured from both ITAs at approximately the same time will be used as the primary outcome measure.

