### Chest wall pain and dysesthesia

Assessments of chest wall pain and dysesthesia will be performed by a blinded observer. A questionnaire, designed to assess differences in pain between the left and right sides, will be administered to patients, and the degree of pain will be quantified using a 100 mm Visual Analog Scale (VAS), which has been used in numerous disciplines to objectively quantify pain. Patients will also be questioned about the quality and the impact of post-operative pain on their daily activities as well as the need for analgesic medication. However, only the VAS quantification of pain will be side-specific.

There is a paucity of data on the optimal methodology for assessing and quantifying post-operative dysesthesia of the chest wall following ITA harvest. In consultation with a pain specialist, we have developed a methodology for the detailed assessment of sensory deficits of the anterior chest wall. A sensory examination will be conducted by a blinded observer employing three different sensory modalities. Deficits in light touch, pinprick sensation, and temperature will be mapped out on a grid (Figure 2) by systematically testing the entire anterior chest wall from the clavicle, superiorly, to the inferior edge of the midline skin incision. These assessments of pain and dysesthesia will be conducted upon discharge (4 – 6 days post-operatively), at 4 weeks, and at 3 months post-operatively.

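### The unblinded-measurement exception for ITA length and the primary direct-flow outcome is wider than its stated reason: timing the collection, reading the cup and measuring the suture could be masked or made independent at little cost

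*Protocol article*

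**What the plan says.** The section Study design, randomization, and blinding sets a general rule: "Assessment of the outcome measures will be performed by individuals blinded to the treatment assignment whenever possible". It then makes an exception. The reason is "Because of the nature of certain endpoints, requiring visual feedback", and the consequence is that "evaluation of ITA length and flow will be performed intra-operatively by individuals performing the ITA harvest who will be aware of the treatment assignment".

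The section Conduit flow shows that the exception reaches the primary outcome: "pre-anastomotic direct flow (before papaverine treatment) measured from both ITAs at approximately the same time will be used as the primary outcome measure". Direct flow is obtained at division of the vessel by "measuring the amount of blood filling a calibrated cup over 15 seconds".

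For length, the section Conduit length says: "A separate silk suture will then be used follow the course of the ITA to measure its length". It adds: "Separate sutures will be used for the left and right sides and labeled in order to avoid misclassification".

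The trial has a masked assessor for other outcomes. Under Chest wall pain and dysesthesia: "Assessments of chest wall pain and dysesthesia will be performed by a blinded observer". That observer works at discharge, 4 weeks and 3 months. No masked reading of cups or sutures is described.

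**The concern.** The justification covers some parts of these measurements and not others. Placing a Doppler probe, laying a suture along an in-situ artery under tension and catching blood from a divided vessel all need someone who sees the field. Timing a fixed interval, reading a volume off a scale and laying a suture against a ruler do not. A filled cup and a length of silk do not show how the artery was harvested. By the protocol's own rule these steps should be masked, or at least taken out of the harvester's hands, where that can be done.

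What is at stake is the primary comparison. Randomizing order, stratifying by side and pairing within patient deal with side, period and patient factors. They do not deal with a measurement error that follows the technique, because such an error enters every paired difference with the same sign. The Introduction and the section Proposed benefits of skeletonization list greater flow and greater length among the proposed benefits, so an expectation in one direction is plausible.

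**Working it through.** **Inputs** (Statistical analysis and sample size calculations, unless noted): 45 pairs; target difference 8 ml/min; mean flow 26.4 ml/min in the non-skeletonized group; SD 16.1, an unpaired SD used in place of the unknown SD of the paired difference; two-sided alpha 0.05; power 90%. Collection time 15 s (Conduit flow). The documents give no size for any reading or timing error, so every error size below is an assumption.

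**1. The plan's own figure.** Normal approximation: n = (16.1 × (1.960 + 1.282) / 8)² ≈ 42.6, so 43. With the exact paired t-test, power is 89.65% at n = 44 and 90.32% at n = 45, so 45 is the smallest n that reaches 90%. The stated 45 reproduces and is not in dispute.

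**2. The target in the cup.** Fifteen seconds is a quarter of a minute.
- Non-skeletonized mean: 26.4 / 4 = 6.6 ml.
- Target difference: 8 / 4 = 2.0 ml.

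**3. What small errors amount to** (assumed sizes).
- One cup collected 1 s too long: 26.4 / 60 = 0.44 ml, recorded as 0.44 × 4 = 1.76 ml/min, which is 1.76 / 8 = 22% of the target.
- Each cup rounded by 0.25 ml in opposite directions: 0.5 ml, or 0.5 × 4 = 2 ml/min, which is 2 / 8 = 25% of the target.

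**4. Effect on the false-positive rate.** Suppose there is no true difference, but a mean error b always favours the same technique. The paired t-test with n = 45 has 44 degrees of freedom and SE = 16.1 / √45 = 2.40. Its rejection probability follows from the noncentral t distribution with noncentrality b / SE. The paired t-test stands in here for the planned 3-way ANOVA; adjusting for stratum and period would not remove an error tied to technique.

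The paired SD is unknown, so two further values are shown. With an SD of 16.1 on each side and an assumed within-patient correlation of 0.7, it is 16.1 × √(2 × 0.3) = 12.5. With correlation 0, it is 16.1 × √2 = 22.8.

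| Differential per cup (ml) | b (ml/min) | SD 12.5 | SD 16.1 | SD 22.8 |
|---|---|---|---|---|
| 0 | 0 | 5.0% | 5.0% | 5.0% |
| 0.25 | 1 | 8.2% | 6.9% | 6.0% |
| 0.5 | 2 | 18.3% | 12.9% | 8.9% |
| 0.75 | 3 | 35.2% | 23.1% | 13.9% |
| 1.0 | 4 | 55.7% | 37.1% | 21.1% |

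The 1.76 ml/min of the one-second example gives 11.1% at SD 16.1, if it occurred on average across all patients. The protocol expects the paired SD to be below 16.1; if so, the same bias does more harm.

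**5. What masking changes.** It leaves the sample size and the 90.3% power as they are. It removes one possible source of bias.

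**The case against.** The strongest reply is that the choice is disclosed and reasoned. The reason is sound for most of the measurement: laying the suture, setting tension, placing the probe and catching the blood all need sight of the vessel. Masked reading leaves those operator-controlled steps as they are, and what it protects, a calibrated volume and a fixed interval, is fairly objective. All of this stands, and it limits how much the change can achieve. It does not show that the reason covers timing, cup reading or suture measurement.

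A reader might also infer more than the documents support:

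- **That the operating surgeon personally times, reads and records the primary outcome.** The text assigns the evaluation to those performing the harvest. The description of the cup method does not say who runs the clock, reads the scale or writes the value, and the intra-operative figure is not available.
- **That the sutures carry nothing but a side label.** The article says they are labelled by side and does not describe the whole label.
- **That a bias exists, or that its direction is known.** The listed benefits make an expectation plausible, but no preference of the two surgeons is stated. Random timing or rounding errors would add noise, not bias.
- **That a masked reader is already in theatre.** The one documented blinded observer works at the postoperative assessments. Presence in theatre is not stated, so masked cup reading may need an extra person.

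One further caution stands. Giving side-labelled sutures to the pain and sensory observer before those assessments are complete could unmask them: greater length with skeletonization is one of the proposed benefits, so the longer suture hints at the side.

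**Conclusion.** The point holds as an avoidable weakness in a stated rule. The protocol departs from its own blinding standard on the primary outcome and on length, and its reason does not cover three separable steps: timing the 15 s, reading the cup and measuring the suture.

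The step from 5% to about 13% rests on an assumed mean differential of 0.5 ml, always favouring the same technique, with 45 pairs and a paired SD of 16.1. At 0.25 ml the rate is 6.9%. These figures show how little blood separates a null result from the target; they do not estimate this trial's error rate. The documents do not show that the primary result will be biased, and the sample size is unaffected. This is a cheap improvement worth making, not a defect that invalidates the design.

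**What to change.** - Narrow the exception under Study design, randomization, and blinding to the steps that need sight of the vessel.
- Have someone other than the harvester, already in theatre, call the start and stop of the 15 s collection from a clock.
- Give each cup a neutral code. Where a staff member already present can be kept unaware of the allocation, have that person read the cups off the field. If nobody can be kept unaware, say so.
- Keep the two sutures per patient under a neutral code, not left and right, and have the existing blinded observer measure them only after that patient's 3-month pain and sensory assessment.
- Acknowledge as a limitation that suture tension, marking of the suture ends, blood collection and the Doppler readings stay unmasked.

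The cost is a small handling step, a code list linking codes to sides, and storage of two sutures per patient. Masked cup reading needs an extra reader only if nobody already present can be kept unaware. Sample size, endpoints and surgical procedure do not change.

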### Outcome measures

The conduct of the intra-operative procedures as well as the intra-operative outcomes is displayed in figure 1.

**Figure 1 F1:**
[figure not shown]
The intra-operative protocol involves measurement of ITA length (in-situ) as well as intra-operative flow measurements on four occasions.

### Conduit length

The length of the harvested ITA will be measured in-situ (i.e. with the proximal and distal ends attached) from the first rib to ITA bifurcation in a standardized fashion. After the conduit has been fully dissected along its entire length and prior to division of its distal end, the midportion will be encircled by a length of sterile silk suture. Uniform tension will be applied to the two ends of the suture. A separate silk suture will then be used follow the course of the ITA to measure its length from the first rib to the ITA bifurcation. Separate sutures will be used for the left and right sides and labeled in order to avoid misclassification.

### Conduit flow

ITA flow will be measured on four separate occasions. The first time point will be immediately following each individual ITA harvest with the vessel in-situ, using a Doppler flow meter (Transonics Inc., Binghamton, NY, USA). The flow probe will be placed at a point approximately halfway between the first rib and the ITA bifurcation. The size of the probe will be chosen by the surgeon to best fit the conduit and the same probe will be used for both ITAs in order to minimize variability and measurement error. The second measurement will be performed after both ITAs have been harvested, are ready for distal division and systemic heparin has been administered. Direct blood flow from each ITA will be measured upon division by measuring the amount of blood filling a calibrated cup over 15 seconds. The ITAs will then be treated with a vasodilator, papaverine, applied topically, in order to eliminate any vasospasm that may occur due to the handling as well as mechanical or thermal trauma to the vessel. The third flow measurement will be performed after a 5–10 minute treatment with papaverine (equal duration of treatment for both ITAs) using the direct flow technique described above. The patient will then undergo coronary artery bypass grafting and the final flow measurement will be performed after all anastomoses have been completed, using the Doppler flow probe.

The amount of flow within a vessel is a function of the systemic blood pressure and the resistance offered by the vessel. In addition, errors in measurement exist with all measuring devices including the transonic Doppler flow probe. Post-anastomotic Doppler flows are further dependent on the size of the outflow vessel, the degree of distal disease and the size and vasoreactive characteristics of the distal myocardial bed that is supplied. Recognizing these potential sources of inaccuracies, pre-anastomotic direct flow (before papaverine treatment) measured from both ITAs at approximately the same time will be used as the primary outcome measure.

### Chest wall pain and dysesthesia

Assessments of chest wall pain and dysesthesia will be performed by a blinded observer. A questionnaire, designed to assess differences in pain between the left and right sides, will be administered to patients, and the degree of pain will be quantified using a 100 mm Visual Analog Scale (VAS), which has been used in numerous disciplines to objectively quantify pain. Patients will also be questioned about the quality and the impact of post-operative pain on their daily activities as well as the need for analgesic medication. However, only the VAS quantification of pain will be side-specific.

There is a paucity of data on the optimal methodology for assessing and quantifying post-operative dysesthesia of the chest wall following ITA harvest. In consultation with a pain specialist, we have developed a methodology for the detailed assessment of sensory deficits of the anterior chest wall. A sensory examination will be conducted by a blinded observer employing three different sensory modalities. Deficits in light touch, pinprick sensation, and temperature will be mapped out on a grid (Figure 2) by systematically testing the entire anterior chest wall from the clavicle, superiorly, to the inferior edge of the midline skin incision. These assessments of pain and dysesthesia will be conducted upon discharge (4 – 6 days post-operatively), at 4 weeks, and at 3 months post-operatively.

**Figure 2 F2:**
[figure not shown]
This diagram depicts the anterior chest wall grid to be used for mapping of sensory deficits. Separate grids will be used for the mapping of defects in light touch, pin-prick, and temperature by a blinded observer and areas of anesthesia and hyperesthesia will be mapped using different symbols.

### Sternal ischemia

A subgroup of patients (n = 15) will be randomly chosen to undergo Single Photon Emission Computed Tomography (SPECT) to assess sternal vascularity. Each study involves complete tomographic imaging of the sternum pre and post operatively (between post-operative days 3 and 5). The scan involves the use of ^99m^Tc labeled methylene diphosphonate, and the results of SPECT imaging will be analyzed as previously using a previously described protocol [6,17], adapted to a paired side to side comparison. The results will be reported as counts/pixel.

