### Statistical analysis and sample size calculations

The patient characteristics will be described using means ± SEM or medians (interquartile range) for normally distributed and skewed data as appropriate. Analysis of all endpoints will be conducted using paired analysis. Continuous variables will be analyzed using 3-way ANOVA, adjusting for stratification and time period variables. Differences in conduit flow (ml/min), length (cm), sternal perfusion (# pixel counts/cm^2^), chest wall pain (VAS score), and area of chest wall dysesthesia (cm^2^) will be analyzed using these methods. In addition, chest wall pain and chest wall dysesthesia will also be dichotomized and analyzed as binary endpoints using McNemar's test. All statistical analyses will be conducted using SAS version 9.1 (SAS Institute, Cary, NC, USA).

For the purpose of sample size calculations, change in ITA flow has been chosen as the primary outcome measure. The reason for this choice is that a) this is a clinically important early endpoint affected by harvesting technique, b) there is some preliminary data available from observational studies evaluating ITA flow, and c) there is a lack of preliminary data regarding other endpoints like chest wall pain and dysesthesia to use for a sample size calculation.

The sample size for this study will be 45 patients i.e. 45 pairs of ITAs. Using direct ITA flow at the second measurement, prior to papaverine application, this study will be powered to detect an absolute difference as low as 8 ml/min between the skeletonized and non-skeletonized ITA flows (30% increase in flow) with the assumption of a mean flow of 26.4 ml/min in the non-skeletonized group[14], at a two-sided alpha level of 0.05 and 90% power. Since the estimate for the standard deviation of the difference between paired samples is not known, the standard deviation between unpaired samples of 16.1 was used to calculate sample size[14]. Since the standard deviation of the difference between paired samples is expected to be less that this value, this likely overestimates the required sample size. There is no anticipated loss to follow-up with respect to the intra-operative ITA flow endpoint.

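### The pre-operative SPECT scan has no stated role in the analysis of sternal perfusion; name it as a covariate and settle the outcome's unit

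*Protocol article*

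**What the plan says.** All of this is in the Protocol article.

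- **Sternal ischemia**, on who is scanned: "A subgroup of patients (n = 15) will be randomly chosen to undergo Single Photon Emission Computed Tomography (SPECT) to assess sternal vascularity".
- Same section, on timing: "Each study involves complete tomographic imaging of the sternum pre and post operatively". The post-operative scan falls on days 3 to 5.
- Same section, on processing: the images are analysed "using a previously described protocol [6,17], adapted to a paired side to side comparison". On the outcome: "The results will be reported as counts/pixel".
- **Statistical analysis and sample size calculations**, on the model: "Continuous variables will be analyzed using 3-way ANOVA, adjusting for stratification and time period variables". Sternal perfusion is then assigned to it by name: "sternal perfusion (# pixel counts/cm^2^), chest wall pain (VAS score), and area of chest wall dysesthesia (cm^2^) will be analyzed using these methods".
- **Paired, within-patient studies in surgery** (Discussion) accepts that the design assumes the left and right arteries are alike before treatment. It says anatomy may call this into question and relies on stratification by side to deal with it.

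No sentence says whether the perfusion response is the post-operative count, a change or a ratio, and none names the pre-operative count as a covariate.

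**The concern.** The statistical section names one model, lists its adjustments and applies it to five outcomes. As described, four of these have no pre-operative measurement: flow and length are measured at operation, pain and dysesthesia from discharge onward. Sternal perfusion is the only one with a baseline, yet it gets the same model and the baseline is not mentioned.

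This matters because of what the paired design leaves in the error. Pairing removes whatever raises or lowers both sides of a patient's sternum together. The side term removes the average left-right difference across patients. Neither removes a left-right asymmetry that belongs to one patient and was there before surgery. The protocol raises left-right difference as a limitation for the arteries, and the pre-operative scan is the measurement that could take it out for the sternum.

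The unit also differs between the two sections: counts per pixel in one, pixel counts per square centimetre in the other. The response variable is therefore defined inconsistently as well as incompletely. At stake is some precision in a 15-patient comparison, and the freedom to choose among a post-operative, change-score or adjusted analysis once the data are seen.

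**Working it through.** **The plan's own figure.** The only sample size given is for direct flow: difference 8 ml/min, SD 16.1, two-sided alpha 0.05, 90% power, 45 pairs.

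- Normal approximation: n = (16.1 × (1.960 + 1.282) / 8)² = 42.6, so 43 pairs.
- Paired t-test: 44 pairs give 89.6% power and 45 give 90.3%.

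The stated 45 is reproduced. It says nothing about SPECT, for which the article gives no power, SD or correlation.

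**Inputs for SPECT.** n = 15 (Sternal ischemia). Two-sided 0.05 and 90% power are borrowed from the flow calculation. The unit is the SD of the post-operative side-to-side difference. The correlation r between a patient's pre- and post-operative side differences is an assumption, so a range is shown. I read the three ANOVA factors as treatment, side and harvest order.

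**Step 1, post-operative difference only.** Fifteen differences less three parameters (treatment, side, order) leave 12 df. From the noncentral t, the detectable difference is 0.913 SD.

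**Step 2, baseline side difference added as a covariate.** This leaves 11 df. Before any gain, the detectable difference is 0.921 SD. Residual variance is multiplied by (1 − r²). Estimating the slope inflates the variance of the treatment contrast by about 1 + 1/(15 − 3 − 2) = 1.10. So:

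detectable difference = 0.921 × √(1.10 × (1 − r²))

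For example, at r = 0.5: 0.921 × √(1.10 × 0.75) = 0.84.

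**Step 3, change score.** If the pre- and post-operative side differences have equal variance, the change has variance 2(1 − r) relative to the post-operative difference. So:

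detectable difference = 0.913 × √(2(1 − r))

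| Assumed r | Post-operative only | Baseline as covariate | Covariate v post-only | Change score |
|---|---|---|---|---|
| 0 | 0.91 | 0.97 | 6% worse | 1.29 |
| 0.3 | 0.91 | 0.92 | 1% worse | 1.08 |
| 0.5 | 0.91 | 0.84 | 8% better | 0.91 |
| 0.7 | 0.91 | 0.69 | 24% better | 0.71 |
| 0.8 | 0.91 | 0.58 | 37% better | 0.58 |

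**Break-even.** Setting steps 1 and 2 equal gives 1 − r² = (0.913/0.921)² / 1.10 = 0.893, so r is about 0.33. Below that the covariate costs slightly more than it returns.

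**Approximation.** The 1.10 is an average for a normally distributed covariate. Fifteen patients cannot split evenly over the four side-by-order combinations, so actual standard errors will be slightly larger under every option.

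**The case against.** The strongest reply is that nothing here is shown to be wrong. A reader might infer that the plan discards the pre-operative counts. The text does not support that: it defers to a cited imaging method, adapted to a side-to-side comparison, immediately after saying that both scans are done. A per-side change or ratio would fit both sections. Silence shows only that the role is unstated. Side-specific baseline counts are likewise implied by whole-sternum imaging and the side-to-side comparison, not stated. This part of the objection stands and limits the point to an unspecified role.

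It can also be said that an article leaves covariates for a secondary endpoint to fuller documents. That has weight. But the article names a model and its adjustments for this outcome and gives two different units for it, so there is a stated analysis to improve and a conflict to resolve.

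On size, three inferences go too far:

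- **Large-sample gains.** The factor √(1 − r²) suggests standard errors 13% and 29% smaller at r = 0.5 and 0.7, worth about 20 and 29 patients. At n = 15, slope estimation and the lost degree of freedom reduce these to 8% and 24%.
- **A free gain.** Adjustment loses a little precision when r is low, and the documents do not say what r is.
- **Only very large effects are detectable.** The 0.91 is in SDs of a paired difference whose value is not given, so it cannot be called large or small in counts.

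Nor does bias follow. Order is randomized with stratification by side, so an unadjusted paired comparison remains valid. If pixel size is fixed, the two units may differ only by a constant and the test would be unchanged; the text should still agree with itself.

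**Conclusion.** The point holds as a modest matter of precision and specification on a secondary endpoint. The article collects a pre-operative scan in 15 patients and gives it no stated role in the model named for sternal perfusion. Compared with analysing post-operative counts alone, using it as a covariate ranges from a 6% loss at r = 0 to a 37% gain in detectable difference at r = 0.8, with break-even near r = 0.33. It clearly beats a change score at low r and matches it at r = 0.8.

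These figures rest on assumed values of r, on 12 against 11 df, on an approximate 1.10 inflation, and, for the change score, on equal pre- and post-operative variances. The mismatch in units needs no assumption but is minor. The primary flow endpoint is unaffected.

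**What to change.** In the statistical section, give sternal perfusion its own sentence, for example: *The post-operative difference in counts between the skeletonized and non-skeletonized sides will be analysed within patient, with the corresponding pre-operative difference as a covariate, together with side and order of harvest.* If the cited imaging method already defines a pre/post measure, say so and state how it enters the model. Fix the choice before any SPECT data are examined.

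Reconcile Sternal ischemia with the statistical section so that one unit is used in both.

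The cost is one degree of freedom and a small loss of precision if r is about 0.3 or less. No extra scan, visit or patient is needed, provided the pre-operative images are read separately by side, which the text implies.
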